### Objectives and endpoints

The primary endpoint is the diagnostic performance of ENB-guided needle biopsy and forceps biopsy and the yield achieved by combining the modalities based on the 12-month clinical follow-up. Secondary endpoints include a comparison of successful approach to the lesion, duration of sampling time, number of attempts, and successful acquisition of core tissue between the needle and forceps biopsy techniques. Additionally, all adverse events related to the ENB procedure or sedatives will be captured and classified according to the Common Terminology Criteria for Adverse Events (CTCAE) scale, version 5.0 [26]. Pneumothorax will be confirmed using chest X-rays performed post-procedurally and the day after the procedure. All participants will be followed up at 2 weeks post-procedure to evaluate the presence of delayed complications. The detailed definitions of outcomes are presented in Table 2.

**Table 2 Tab2:** Definitions and overview of study endpoints

Primary endpoint: diagnostic values
- Primary endpoints will be calculated separately for needle aspiration, forceps biopsy, and the combination of the two. For initially negative results, the final diagnosis will be confirmed based on the 12 months of clinical follow-up
- Diagnostic accuracy:
Proportion of subjects in whom the ENB-guided biopsy yielded a definite diagnosis = (malignant and benign diagnosis by modality)/(biopsied lung lesions)
- Sensitivity:
= (Malignancy confirmed by modality)/(Number of malignancies confirmed at 12-month follow-up)
- Specificity:
= (Benign confirmed by modality)/(Number of benign lesions confirmed at 12-month follow-up)
- Positive predictive value:
= (True malignant lesions)/(Number of malignant lesions by modality)
- Negative predictive value:
= (True benign lesions)/(Number of benign lesions by modality)

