**Methods:**

The trial will recruit 142 participants with lung lesions suspected of malignancy who are eligible for an elective ENB procedure under moderate sedation. Participants will undergo ENB-guided needle aspiration and forceps biopsy in a randomized order without the use of any complementary techniques. All participants will be followed up subsequently for up to 12 months to conclude the final diagnosis of the biopsied lesions. Primary outcomes include the diagnostic yield and sensitivity of each biopsy modality and the diagnostic yield of the combined modalities.

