### Diagnosis and follow-up

All cases with histopathologically confirmed malignancy based on either ENB-guided needle biopsy or cytology, forceps biopsy, or BAL cytology are determined as positive for malignancy. The histopathological results of the biopsied samples that reveal no malignancy or indeterminate findings are initially considered negative. In such cases, the attending physician will conduct follow-up for at least 12 months and make decisions to perform additional invasive procedures to determine the true diagnosis (gold standard) accordingly. The final diagnosis will be determined at 12 months from the procedure. The following cases will be defined as false negatives: (1) malignancy based on a repeat biopsy (e.g., surgical biopsy, CT-guided TTNA, and bronchoscopic); (2) growth of the lesion observed on serial follow-up CT within 12 months; (3) treated as lung cancer without pathological confirmation; and (4) lung cancer diagnosed at other sites (including non-index lesions or lymph nodes diagnosed using linear EBUS during or after the index procedure) within 6 months. The following cases will be defined as true negatives: (1) subsequent diagnostic procedures confirm a non-malignant diagnosis; (2) an initial non-malignant lesion resolved without cancer treatment (e.g., improved proven infectious disease or transient inflammation); or (3) no lesion progression observed on radiographic follow-up for 12 months.

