### Primary statistical plan and sample size considerations

The sample size was calculated in order to determine a 15% difference in the diagnostic yield between the individual modalities and their combined use owing to the expected better and synergistic diagnostic yield. The estimated difference in the diagnostic yield (67% vs. 82%) is based on previously conducted large-scaled observational studies and meta-analyses that suggested an improved diagnostic yield with the use of needle aspiration and a combination of both modalities [11, 12, 14, 16]. The calculation was based on this difference in the diagnostic accuracy for equality of paired proportions with a two-sided significance level of 0.05 and 80% power. Assuming that the response with needle biopsy is independent of the response with forceps biopsy, the percentage of participants with discordant results for the two modalities was estimated to be 39%. With an estimated dropout rate of 5% due to the loss of patients during follow-up, we estimated a sample size of 142 participants (71 in each group, and 142 biopsies for each modality and combination). The sample size was calculated using PASS 2021 (NCSS, LLC., Kaysville, UT, USA).

Baseline demographic, clinical, and radiological characteristics of the participants as well as the procedural details and outcomes will be presented as means with standard deviation (SD) for continuous data and frequencies with proportions for categorical data. Characteristics will be analyzed using the *t*-test (or Wilcoxon’s rank-sum test) for continuous variables and the chi-square test (or Fisher’s exact test) for categorical variables. Since each patient will have two results from separate modalities, it should be considered that two outcomes from the same patient are likely to be more similar than two results from different patients. To compare the paired proportions, McNemar’s test will be used. A *p*-value < 0.05 indicates statistical significance. All analyses will be performed using STATA version 16.0 (StataCorp., College Station, TX, USA). A preliminary analysis is prespecified when all the enrolled participants undergo ENB with available initial pathological reports and 1-month follow-up.

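### The article gives three different sets of primary measures, and PPV and specificity in Table 2 do not work as accuracy measures as defined

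*Protocol article*

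**What the plan says.** The primary measures are stated in three places in the protocol article.

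- **Abstract, Methods:** "Primary outcomes include the diagnostic yield and sensitivity of each biopsy modality and the diagnostic yield of the combined modalities".
- **Objectives and endpoints, text:** diagnostic performance for each of the two tools, but only yield for their combination.
- **Objectives and endpoints, Table 2:** five measures under the primary heading (accuracy, sensitivity, specificity, PPV, NPV), with the instruction "Primary endpoints will be calculated separately for needle aspiration, forceps biopsy, and the combination of the two".

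The section on the statistical plan and sample size sizes the trial on yield, 67% versus 82%, for single versus combined use, "with a two-sided significance level of 0.05 and 80% power". It names McNemar's test for paired proportions and gives one general 0.05 threshold.

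Diagnosis and follow-up sets the reference standard. Cases with malignancy on needle biopsy or cytology, "forceps biopsy, or BAL cytology are determined as positive for malignancy". Non-malignant and indeterminate results both start as negative and are resolved over 12 months. The section defines false and true negatives but no false positive. Table 2 defines specificity as "Benign confirmed by modality)/(Number of benign lesions confirmed at 12-month follow-up".

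On timing, the plan adds: "A preliminary analysis is prespecified when all the enrolled participants undergo ENB with available initial pathological reports and 1-month follow-up".

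**The concern.** A reader cannot tell from the article which measure and which contrast decide the trial. If the tools differ on one measure and not on another, the three lists allow different accounts of whether the primary endpoint was met.

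Separately, two measures labelled primary cannot do what their names suggest. A PPV that the reference standard fixes at 100% says nothing about either tool, yet it would be reported as a result. A specificity that is 100% on one reading and perhaps 35% on the other could not be compared with published values, and on the lower reading it would suggest false positives that did not occur.

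**Working it through.** **1. The plan's own figure.** Inputs from the sample-size section: difference d = 0.82 − 0.67 = 0.15, discordance D = 0.39, two-sided α = 0.05, power 80%, dropout 5%.

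n = [1.960·√D + 0.8416·√(D − d²)]² / d² = [1.960·0.6245 + 0.8416·0.6062]² / 0.0225 = 133.7, so 134.

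134 / 0.95 = 141.1, so 142. The stated size reproduces, and the measure it rests on is yield. (The discordance is described for the two single tools while the target is single versus combined. That is a separate matter and does not change which measure was powered.)

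**2. Size of each primary set.**

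| Place | Measures | Count |
|---|---|---|
| Abstract | yield and sensitivity for 2 tools, plus combined yield | 2×2 + 1 = 5 |
| Text above Table 2 | if performance means Table 2's five measures: 5 for 2 tools, plus combined yield | 5×2 + 1 = 11 |
| Table 2 | 5 measures for 3 strategies | 15 |
| Sample size | yield, single versus combined | 1 measure |

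**3. PPV.** Table 2 divides true malignant lesions by lesions the modality called malignant. Under Diagnosis and follow-up, every lesion in that denominator is malignant by rule, so PPV = 1 for needle, forceps and the combination. A simulation (5,000 trials of 135 lesions; assumed 70% malignant, 67% sensitivity per tool, 3% biological false positives) gave a minimum PPV of 1.000. Even real false positives cannot lower it.

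**4. Specificity, two readings.**

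- *Every non-malignant or indeterminate result is negative* (Diagnosis and follow-up). A lesion finally benign cannot have had a malignant index result, so specificity = 1. The same simulation gave a minimum of 1.000.
- *A definite benign diagnosis by the modality is required* (Table 2's numerator, read with its accuracy row, which counts definite diagnoses). Assume 75% malignancy and a 35% definite-benign rate. Of 135 lesions about 34 are benign (135 × 0.25), of which about 12 get a definite benign result (34 × 0.35). The ratio is 12/34 = 35%, with no false positive. The other 22 are non-diagnostic samples scored as errors.

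**5. Predictive values between tools.** The denominators of PPV and NPV are each tool's own positive or negative calls. In the simulation of step 3 these counts differed between needle and forceps in 94% of trials. They are not proportions on one common set of lesions, so McNemar's test would not compare them.

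**6. Error rate if several measures are tested.** Needle versus forceps with equal tools, 135 evaluable (142 × 0.95 = 134.9), each test at 0.05. Assumed, not in the article: sensitivity 70%, definite-benign rate 35%, within-lesion latent correlation 0 to 0.8, and malignancy 60-75% for the asymptotic test and 60-90% for the exact test.

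| Chance of at least one false claim | Asymptotic McNemar | Exact McNemar |
|---|---|---|
| Yield or sensitivity | about 7-9% | about 4-6% |
| With Table 2 specificity (second reading) added | about 10-12% | about 4-8% |

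The article does not say which version of the test applies.

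**The case against.** Table 2 says its measures are calculated, not that each is tested, and the 0.05 threshold is one general sentence. A reader might infer fifteen tests at 0.05 and, treating them as independent, an error rate of 1 − 0.95^15 = 54%. The document does not support that. Three values per measure are estimates rather than three tests, the measures are correlated, and a PPV fixed at 100% cannot produce a false claim. With the exact test the inflation may be close to nil. This objection stands, so multiplicity is not the main point.

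Three other strong readings also go too far:

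- **Specificity is 100% by construction.** This is true on one of two readings only. On the other the ratio can differ between tools and carries information, though not about specificity.
- **McNemar's test is misapplied to predictive values.** The plan names it for paired proportions and never assigns it to PPV or NPV. A method for comparing those may sit in the full analysis plan.
- **The 1-month analysis already tests the primary endpoint.** It is called preliminary, with no test, stopping rule or claim attached, and the primary endpoint is tied to 12 months. Yield as defined would, however, be largely known by then.

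It can also be said that the abstract's list is introduced by a word that leaves it open, and that the abstract has all participants followed up. An open list still does not say what decides the trial, and no rule lets follow-up overturn a malignant index result.

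**Conclusion.** The point holds in a limited form. On the article's own text there are three primary sets (5, 11 on one reading, and 15 quantities) against one powered measure. PPV is 100% for every strategy by rule. Specificity is either 100% by rule or a benign yield under the wrong name, and the two sections must be reconciled. None of this depends on an unseen analysis plan or on any assumed figure.

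The 35% example and all the error rates rest on assumptions about malignancy prevalence, definite-benign rate and correlation that the article does not give. They show scale only. The stated sample size of 142 is not in question here.

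**What to change.** 1. Name diagnostic yield, combination versus each single tool, as the primary comparison, and align the abstract, the endpoint text and Table 2 to it. Use one term for the measure, since Table 2 calls the same ratio accuracy.
2. Say how the two comparisons (against needle, against forceps) are handled. A fixed order keeps 0.05 for the first and leaves the 142 unchanged. Splitting α would need [2.241·0.6245 + 0.8416·0.6062]² / 0.0225 = 162.1, so 163 evaluable and 163 / 0.95 = 172 enrolled.
3. Report sensitivity and NPV as secondary, with confidence intervals. If NPVs are compared between tools, use a method for paired predictive values, such as a generalised score test.
4. Drop PPV and specificity as primary measures. If PPV is kept, report it as assumed to be 100% with positives not verified. If definite benign diagnoses are meant, rename the specificity ratio specific benign yield.
5. State that the 1-month analysis is descriptive and that conclusions come from the 12-month analysis.

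The cost is wording in the protocol and analysis plan and a registry update. Fewer measures can be called primary, including sensitivity, which the abstract now names. Keeping sensitivity as a second primary measure would be defensible if its place in the testing order were fixed.

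### Table 2 builds specificity and NPV on benign results by modality, which leaves out indeterminate samples that the protocol elsewhere scores as negative

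*Protocol article*

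**What the plan says.** Under the heading "Primary endpoint: diagnostic values", Table 2 (Objectives and endpoints) lists five measures, each to be calculated for needle, forceps and the combination. Three lines matter here:

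- Diagnostic accuracy is the proportion in whom the biopsy "yielded a definite diagnosis = (malignant and benign diagnosis by modality)/(biopsied lung lesions".
- Specificity is "Benign confirmed by modality)/(Number of benign lesions confirmed at 12-month follow-up".
- NPV is "True benign lesions)/(Number of benign lesions by modality".

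The Diagnosis and follow-up section sets the rule for a negative sample: "The histopathological results of the biopsied samples that reveal no malignancy or indeterminate findings are initially considered negative". Follow-up then divides these negatives into false and true negatives. A true negative needs no benign diagnosis from the tool, since "no lesion progression observed on radiographic follow-up for 12 months" is sufficient. Cases with malignant pathology "are determined as positive for malignancy", and no follow-up criterion is given that could overturn such a result. Table 2 refers to the same process: "For initially negative results, the final diagnosis will be confirmed based on the 12 months of clinical follow-up".

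**The concern.** The accuracy row uses a benign diagnosis by modality to mean a definite diagnosis, which an indeterminate sample is not. If the term keeps that meaning in the specificity and NPV rows, both measures use a narrower class of results than the negatives defined under Diagnosis and follow-up.

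Two things are at stake. A tool that returns more indeterminate samples in benign lesions would show a lower specificity without a single false-positive call, and this would enter the needle-forceps comparison. The NPV would describe only definite benign reports, although a clinician given a negative ENB result may well be holding an indeterminate one.

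**Working it through.** **The plan's own figure.** The documents give no expected specificity or NPV. The stated sample size reproduces and uses neither:

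- Discordance under independence: 0.67 × 0.18 + 0.82 × 0.33 = 0.391, the stated 39%.
- n = [1.96·√0.39 + 0.84·√(0.39 − 0.15²)]² / 0.15² = 133.7, rounded up to 134.
- 134 / 0.95 = 141.1, rounded up to 142.

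**The two rules side by side**, with benign by modality meaning a definite benign diagnosis, as in the accuracy row:

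| Sample | Status at 12 months | Follow-up rule | Table 2 specificity | Table 2 NPV |
|---|---|---|---|---|
| Definite benign | Benign | True negative | Numerator and denominator | Numerator and denominator |
| Indeterminate | Benign | True negative | Denominator only, like a false positive | Not counted |
| Definite benign | Malignant | False negative | Numerator only, if taken literally | Denominator only |
| Indeterminate | Malignant | False negative | Not counted | Not counted |

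**Formulas.** Let B be lesions benign at 12 months, M malignant lesions, FN cancers missed by the tool, b the share of B given a definite benign label, and f the share of FN given one. Malignant pathology is final, so there are no false positives.

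- Follow-up rule: specificity = B/B = 100%; NPV = B/(B + FN).
- Table 2: specificity = b with the numerator limited to truly benign lesions, or (bB + f·FN)/B taken literally; NPV = bB/(bB + f·FN).

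The two NPVs agree when b = f. Table 2 is too high when b > f and too low when b < f.

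**Illustration for one tool.** From the plan: 142 × 0.95 ≈ 135 evaluable and a 67% yield, so TP + bB + f·FN = 0.67 × 135 = 90.45. Assumed: 70% malignant, so M = 94.5 and B = 40.5.

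*Case 1, b = 0.4 and f = 0.1 (assumed).* TP + 16.2 + 0.1(94.5 − TP) = 90.45 gives TP = 72 and FN = 22.5.

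- Specificity: 16.2/40.5 = 40% (literal numerator: 18.45/40.5 = 45.6%), against 100%.
- NPV: 16.2/18.45 = 87.8%, against 40.5/63 = 64.3%.

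*Case 2, b = 0.2 and f = 0.4 (assumed).* TP + 8.1 + 0.4(94.5 − TP) = 90.45 gives TP = 74.25 and FN = 20.25.

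- Specificity: 8.1/40.5 = 20% (literal: 16.2/40.5 = 40%), against 100%.
- NPV: 8.1/16.2 = 50%, against 40.5/60.75 = 66.7%.

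**Range.** With prevalence 60 to 80%, b 0.2 to 0.6 and f 0 to 0.2, literal specificity runs from 20% to 91% and NPV is 0 to 56 points too high; f never exceeds b in that grid, so it cannot show the opposite error. With 94 malignant lesions (63 detected, 31 missed), 41 benign, b from 25% to 100% and f from 0 to 50%, Table 2 NPV runs from 39.8% to 100%, against 41/72 = 56.9%.

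**The wider reading.** Suppose benign by modality means any result without malignancy. In Case 1:

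- NPV = 40.5/63 = 64.3%, which is correct.
- Specificity taken literally = 63/40.5 = 156%, because the numerator is not limited to truly benign lesions.
- Accuracy = (72 + 63)/135 = 100%, and it would be 100% for any tool.

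**The case against.** The strongest reply is that Table 2 is shorthand. A specificity numerator is by convention a subset of its denominator, and the sensitivity line is written just as loosely. The note that initially negative results are settled at 12 months points to the true and false negatives of the follow-up section. Read as negative by the tool and benign at 12 months, the lines give the standard measures. The positive rule there is also set per case (needle, forceps or BAL cytology), and the negative rule serves to trigger follow-up, so applying them to each modality is partly inference.

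Much of this is fair. But Table 2 does not state the charitable reading, and that reading gives benign by modality one meaning in the accuracy row and another in the specificity and NPV rows. The inference is also short: true and false negatives are defined for the samples called negative, and Table 2 relies on the same follow-up.

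The reply does rule out some stronger conclusions that a reader might draw:

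- That both measures are wrong on every reading. The wider reading gives a correct NPV.
- That NPV is always overstated. The direction depends on b against f, and the documents give neither.
- That a specificity above 100% would be reported. It shows only that the literal numerator is unrestricted, and an analyst would notice it.
- That a low specificity must be taken for false positives. PPV stands in the same table and would show none.

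**Conclusion.** The inconsistency is real. No single meaning of benign by modality works for the whole of Table 2: the definite-diagnosis meaning turns specificity into a benign-diagnosis yield and drops indeterminate negatives from NPV, while the wider meaning repairs NPV but leaves the specificity numerator unrestricted and makes accuracy trivially 100%.

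The size cannot be fixed from the documents, which give no prevalence, indeterminate rate or mislabelling rate. In the two assumed cases specificity falls from 100% to 40% or 20% (numerator limited to truly benign lesions), and NPV is 23.5 points too high or 16.7 points too low. With no indeterminate results, and the numerator so limited, the two scorings agree.

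The reach is limited. A reader might infer that the main comparison or its power is in doubt, but yield, sensitivity, the sample size and McNemar's test do not depend on these lines. The abstract names only yield and sensitivity as primary outcomes, although Table 2 places specificity and NPV under the primary heading too. This is worth correcting before the 12-month analysis.

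**What to change.** In Table 2, for each modality and the combination, define:

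- Specificity = (lesions benign at 12 months with no malignant result by the modality) / (all lesions benign at 12 months).
- NPV = (lesions benign at 12 months with no malignant result by the modality) / (all lesions with no malignant result by the modality, indeterminate included).

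Keep the definite benign diagnosis for the accuracy row. If its share among benign lesions is of interest, report it separately under its own name. Add a note that specificity will be about 100% by construction, because malignant pathology is taken as final, and so will hardly separate the tools.

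The cost is two reworded lines and a note, in Table 2 or the analysis plan. No new data are needed and the sample size stays at 142. The reported NPV may move in either direction.

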**Secondary endpoints**
- Secondary outcomes will be calculated separately for needle aspiration and forceps biopsy
- Navigation success:
Target lesion successfully reached with the biopsy tool; identified by the dedicated navigation software
- Procedure time:
Duration from the initial introduction of the tool to the final removal of the biopsy tool
- Time per biopsy attempt:
Procedure time divided by the number of biopsy attempts
- Successful acquisition of core tissue:
Acquisition of a fresh tissue available for histological examination
Procedure-related adverse events
-Pneumothorax
Grade 1: asymptomatic; clinical or diagnostic observations only; intervention not indicated
Grade 2: symptomatic; intervention indicated (e.g., thoracic tube insertion without pleurodesis)
Grade 3: pleurodesis and/or operative intervention indicated; hospitalization indicated
Grade 4: life-threatening consequences; urgent intervention indicated
Grade 5: death
Bronchopulmonary hemorrhage
Grade 1: mild symptoms: intervention not indicated
Grade 2: moderate symptoms: invasive intervention not indicated
Grade 3: transfusion indicated; invasive intervention indicated; hospitalization
Grade 4: life-threatening consequences; intubation or urgent intervention indicated
Grade 5: death
Respiratory failure:
Life-threatening situations with urgent intubation or ventilator support indicated

*ENB-guided biopsy* Electromagnetic navigation bronchoscopy-guided biopsy

